## Abstract

**Background:**

Neck and upper limb symptoms are frequently reported by computer workers. Work style interventions are most commonly used to reduce work-related neck and upper limb symptoms but lifestyle physical activity interventions are becoming more popular to enhance workers health and reduce work-related symptoms. A combined approach targeting work style and lifestyle physical activity seems promising, but little is known on the effectiveness of such combined interventions.

**Methods/design:**

The RSI@Work study is a randomised controlled trial that aims to assess the added value of a lifestyle physical activity intervention in addition to a work style intervention to reduce neck and upper limb symptoms in computer workers. Computer workers from seven Dutch companies with frequent or long-term neck and upper limb symptoms in the preceding six months and/or the last two weeks are randomised into three groups: (1) work style group, (2) work style and physical activity group, or (3) control group. The work style intervention consists of six group meetings in a six month period that take place at the workplace, during work time, and under the supervision of a specially trained counsellor. The goal of this intervention is to stimulate workplace adjustment and to improve body posture, the number and quality of breaks and coping behaviour with regard to high work demands. In the combined (work style and physical activity) intervention the additional goal is to increase moderate to heavy physical activity. The control group receives usual care. Primary outcome measures are degree of recovery, pain intensity, disability, number of days with neck and upper limb symptoms, and number of months without neck and upper limb symptoms. Outcome measures will be assessed at baseline and six and 12 months after randomisation. Cost-effectiveness of the group meetings will be assessed using an employer's perspective.

**Discussion:**

This study will be one of the first to assess the added value of a lifestyle physical activity intervention in addition to a work style intervention in reducing neck and upper limb symptoms of computer workers. The results of the study are expected in 2007.

## Background

### Introduction

Neck and upper limb symptoms are frequently reported by computer workers. More than 50% of the computer workers report symptoms in neck, shoulders, arms, wrists or fingers [1]. In the year 2002, 28% of the general Dutch working population suffered from pain or stiffness in the neck, shoulder, arms, hands or wrists in the previous 12 months [2]. In Europe the prevalence for work-related neck/shoulder pain was 25% and 15% for work-related arm pain [3]. The total yearly costs of neck and upper limb symptoms in the Netherlands due to decreased productivity, sick leave, chronic disability for work and medical costs were recently estimated at 2.1 billion euros [4].

Several names have been used to indicate symptoms in neck, shoulders, arms, hands or wrists. The most commonly used names are cumulative trauma disorders (CTDs), musculoskeletal disorders (MSDs), upper limb disorders (ULDs), upper extremity disorders (UEDs) and repetitive strain injury (RSI). In October 2004 the name CANS has been introduced in the Netherlands to indicate complaints in arm, neck and shoulder. However, since the general Dutch population is more familiar with the name RSI, the name of the present study is RSI@Work study. This study deals with non-specific work-related neck and upper limb symptoms.

### Rationale behind the study

The general model behind the present study is the dynamic model of workload presented by Van Dijk et al. [5]. According to this model, health effects may result from an imbalance between workload and capacity. By increasing capacity and decreasing workload this imbalance may be restored. The present study is designed to assess the effectiveness of an intervention that intends to decrease workload by improving work style and to increase capacity by improving general physical activity of computer workers with neck and upper limb symptoms. By comparing the effectiveness of a combined intervention (work style and physical activity) with a single intervention (work style) and a control intervention (usual care), the added value of a lifestyle physical activity intervention in addition to a work style intervention will be assessed. In addition, the effectiveness of a combined and single intervention will be compared with the effectiveness of usual care. Although general capacity is the result of physical as well as mental capacity, the RSI@Work study will primarily focus on the physical component.

In order to reduce workload, we will use a multidisciplinary approach to improve work style. The concept of work style was constructed by Feuerstein et al. [6] and represents the individual responses to high work demands. In the present study we defined work style as the following three individual responses to high work demands: 1. optimal body posture and proper workplace adjustment, 2. the number and quality of breaks and 3. coping with high work demands. The general idea is that, in case of high work demands, workers will be less inclined to pay attention to their body posture, adjust their workplace properly and use break and exercise reminder software.

In order to improve physical capacity, workers are stimulated to increase their general physical activity by means of active commuting, sports, and daily physical activities at work and/or during leisure time. Increasing physical activity might be effective in reducing neck and upper limb symptoms through three different mechanisms. The first mechanism is based on the improvement of muscle functioning. In a study with neck and shoulder myalgia, Kadi et al. [7] showed an increase in oxidative capacity (i.e. capillary density) and muscle functioning of the trapezius muscle resulting from strength and endurance training. High oxidative capacity may prevent high calcium levels and mitonchondrial damage resulting from continuous activation of type 1 muscles during computer work. The second mechanism is based on a discontinuation of repetitive movements during computer work by physical activity at the workplace. Byl et al. [8] showed changes in the central nervous system and motor deterioration in owl monkeys performing "highly articulated" repetitive movements in precision tasks. Changes in the central nervous system as described by Byl et al. [8] may underlie neck and upper limb symptoms in computer workers. The third mechanism is based on the role of physical activity in coping with high work demands and stress. Physical activity stimulates muscle relaxation after physical exertion and can distract workers from stressful work aspects. Furthermore, physical activity may reduce stress through increased self-efficacy and self-esteem [9].

Several studies have been published on the effectiveness of exercise programs to reduce pain and disability in patients with neck and shoulder symptoms [10-22]. Many of these studies showed positive effects on the reduction of neck and/or shoulder symptoms [10,14,16,17,19-22] but not all [11-13,15,17,18]. However, most of these studies show only short-term effects of exercise programs [10,14,17,19,21]. Long-term adherence to exercise programs is often low, possibly due to lack of pleasure or high barriers to visit a health club [20]. Pleasure seems to be an important predictor of walking, moderate intensity and strenuous intensity physical activity [23]. Lifestyle physical activity interventions that aim to increase physical activity up to at least 30 minutes per day seem to be promising with regard to the maintenance of physical activity [24]. In contrast to exercise programs, the primary goal of lifestyle physical activity interventions is to integrate moderate intensity physical activities into daily life [24]. A key feature of lifestyle physical activity interventions is that physical activities are not prescribed but chosen by the participants.

## Methods/design

### Design and study population

The RSI@Work study is a Randomised Controlled Trial (RCT) with two intervention groups and a control group, an intervention period of six month and measurements at baseline and after six and 12 months of follow-up. Computer workers (N = ± 8000) from the head-offices of 7 Dutch companies in various branches (e.g. insurance, science, energy, transportation-policy and taxes) in different regions of the Netherlands received a short questionnaire about symptoms (i.e. pain, stiffness, tingles) in neck, shoulders, arms, wrists and hands in the past two weeks and the past six months. Furthermore they received written information about the study, and a letter in which they were requested to fill out the questionnaire and send it to the researchers. At the end of the short questionnaire, workers could indicate whether or not they were willing to participate in the study. The researchers used the short questionnaire to select workers who were eligible for participation in the study. The following inclusion criteria were used:

1) Frequent (i.e. at least once a week) or long term pain, stiffness or tingles in neck, shoulders, arms, wrists and/or hands in the preceding six months and/or the last two weeks. By using a six-month period and a two-week period, we intend to include workers with chronic and recurrent symptoms as well as workers with recent symptoms.

2) Performing computer work for at least three days a week during at least three hours a day.

3) A working contract until the last follow-up measurement.

4) Not under treatment of a doctor or (physical) therapist for complaints in the neck, shoulders arms, wrists and/or hands.

5) No non-work related or clear somatic diseases (e.g. rheumatoid arthritis, cervical hernia, tennis elbow, carpal tunnel syndrome).

6) Sickness absence of less than 50%.

Women who were pregnant at the start of the study were excluded since they were unable to complete the study due to their pregnancy leave. Workers who met all inclusion criteria and were willing to participate in the study received a written informed consent, a baseline questionnaire, a short medical questionnaire and an invitation to participate in the baseline measurements. The baseline measurements consisted off a submaximal cardiorespiratory fitness test, a measurement of body height and body weight, a maximum grip strength test and a workplace observation. The baseline measurements were conducted within one month after receiving the baseline questionnaire. At the day of the baseline measurements the workers handed over their completed questionnaire and written informed consent to the researchers. Workers who were unable to participate in the baseline measurements were asked to send their completed baseline questionnaire and informed consent to the VU university medical center. All workers who gave informed consent and completed the baseline questionnaire were randomised into one of the two intervention groups (1. the work style group, 2. the work style plus physical activity group) or the control group.

The study was approved by the Medical Ethics Committee of the VU University Medical Center (number 04/027) and all participants provided written informed consent. In May/June 2003 a pilot study was performed in three companies. The goal of this pilot study was to practice, evaluate and adjust the RSI@Work intervention. On the basis of the results of this pilot, small improvements in the design have been made to ensure the feasibility of the study in companies. The baseline measurements and follow-up measurements were conducted in October 2004 (T_0_), April 2005 (T_1_) and October 2005 (T_2_). The results of the RSI@Work study are expected in 2007.

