### Sample size and participant flow

The main primary outcome variable in this study is self-reported recovery. The intervention will be considered successful if recovery from work-related neck and upper limb symptoms (i.e. completely recovered or much recovered) is 20% higher in the intervention group than in the control group. The number of participants in each group needed to detect a difference in recovery of 20% between the intervention group and the control group was ± 80, with α = 0.05 (two sided) and β = 0.20. This number was based on our expectation that recovery would be 80% in the intervention group and 60% in the control group. However, since we expected a loss-to-follow-up of 40%, ± 135 workers were needed in each group at baseline. Based on our pilot study we expected that 6.25% of our source population would participate in the study, which brings the minimum number of workers that needed to be invited for participation at 6480 workers. Figure 1 shows that approximately 8000 workers were invited to participate and that 466 workers were randomised into the trial.

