
### Measurements

All outcome variables, except for degree of recovery and body height, will be assessed three times: prior to the start of the intervention (T0), at the end of the six month intervention (T1) and 12 months after the start of the intervention (T2). Degree of recovery is assessed at T1 and T2 and body height is measured at baseline only.

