### Data analysis

Intention-to-treat analyses will be used to estimate the effect of the intervention. Multilevel analyses will be used to investigate differences in recovery and changes in outcome variables between the intervention groups and the control group after six months and one year of follow-up. Multilevel analyses are used in order to adjust for possible dependency between observations from the same company.

Cost-effectiveness ratios will be calculated by dividing the difference between the mean costs by the difference in the mean effects in the primary outcome variables. Bootstrapping will be used to calculate the confidence intervals for the cost-effectiveness ratios. Ratios will be graphically presented on a cost-effectiveness plane. Furthermore, acceptability curves will be calculated for both interventions showing the probability of being cost-effective a specific ceiling ratio.

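### Optional improvement: adjust the recovery comparison for baseline pain and symptom days, which are already collected, and report a standardised difference in recovery percentage

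*Protocol article*

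**What the plan says.** All references are to the protocol article.

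- **Population** (Design and study population). Symptoms qualify in the preceding six months and/or the last two weeks, with a stated purpose: "we intend to include workers with chronic and recurrent symptoms as well as workers with recent symptoms".
- **Allocation** (Treatment allocation). Strata are company and baseline sports participation, with blocks of three. No symptom measure is a stratification factor.
- **Main outcome** (Sample size and participant flow). "The main primary outcome variable in this study is self-reported recovery". Success is a 20-point higher recovery percentage.
- **Timing** (Measurements). "Degree of recovery is assessed at T1 and T2". Pain intensity, disability, symptom days and symptom-free months are also measured at T0, the baseline.
- **Analysis** (Data analysis). "Multilevel analyses will be used to investigate differences in recovery and changes in outcome variables between the intervention groups and the control group". The reason given for multilevel models is dependency between workers of the same company.
- **Other adjustment** (Co-intervention and compliance). Actions taken against symptoms during the study are recorded so that they can be adjusted for. These arise after randomisation.

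No section lists baseline covariates for the recovery model, and none says that there are none.

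**The concern.** The other primary outcomes use baseline information because they are analysed as changes. Recovery cannot be analysed that way, since it is rated only at follow-up. In a population mixed by design, baseline symptom burden may well predict who recovers, and allocation does not balance it.

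At stake is efficiency on the outcome that decides success. Prognostic variation left unexplained widens the interval for the recovery difference. Chance imbalance in symptom burden also shifts the estimate in the one trial that is run. The baseline questionnaire had to be completed before randomisation, so the covariates should be nearly complete.

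**Working it through.** **1. The plan's own figure.** Inputs from Sample size and participant flow: "recovery would be 80% in the intervention group and 60% in the control group", "with α = 0.05 (two sided) and β = 0.20".

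- Pooled variance, mean proportion 0.70: n = [1.960 × √(2 × 0.70 × 0.30) + 0.842 × √(0.80 × 0.20 + 0.60 × 0.40)]² / 0.20² = (1.270 + 0.532)² / 0.04 = 81.2, so 82 per group.
- Unpooled variance: n = (1.960 + 0.842)² × 0.40 / 0.04 = 78.5, so 79.
- Arcsine: about 80.

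The stated ± 80 reproduces as an unadjusted comparison of two proportions. With 40% loss, 80/0.60 gives 134 and 82/0.60 gives 137, against the stated ± 135. The 466 randomised give 466/3 = 155 per group, and 155.3 × 0.60 = 93 evaluable.

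**2. Effect of adjustment on the risk-difference scale.** The approximation multiplies the variance by (1 − R²), where R² is the share of recovery variance explained by the baseline data. The article gives no R², so these values are assumptions.

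| Assumed R² | Power, 80 per arm | Power, 93 per arm | n per arm for 80% power |
|---|---|---|---|
| 0 | 79.4% | 85.1% | 82 |
| 0.05 | 81.4% | 86.9% | 78 |
| 0.10 | 83.5% | 88.6% | 74 |
| 0.20 | 87.6% | 91.9% | 66 |

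**3. Simulation of the proposed estimator.** Recovery was generated from a logistic model with one standard normal baseline score, with marginal recovery of 60% and 80% and 80 per arm. The adjusted model also carried three pure-noise covariates, and the test was on the standardised risk difference. For log odds ratios of 0.5 to 1.3 per SD (R² about 0.05 to 0.24), power rose from about 80% to 82–88%. With no prognostic value at all, adjustment cost about one point. The simulation did not include clustering by company.

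**4. The Wald test in a logistic model.** Tested on the log odds ratio with one covariate, adjusted power was 0.80, 0.84, 0.86 and 0.89 for log odds ratios of 0.5, 0.7, 1.0 and 1.3 per SD, against about 0.80 unadjusted. The standard error does not shrink on this scale: it rose from 0.37 to 0.39–0.41 for odds ratios of 2.0 to 2.7 per SD. The power comes from a conditional odds ratio further from 1. A gain in precision can be claimed only for the standardised difference.

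**5. Chance imbalance, as illustration.** Assume that half the workers have long-standing symptoms. With 80 per arm, the SD of the between-arm difference in that share is √(2 × 0.25/80) = 7.9 points, so a difference of 10 points or more in either direction has probability of about 21%. If recovery differed by an assumed 30 points between the two kinds of worker, a 10-point imbalance would move the estimate by 0.10 × 30 = 3 points, against the 20-point criterion.

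**The case against.** A reader might infer that the recovery model leaves out all baseline symptom data, and that this is a flaw. The article does not support that. Its remark about company explains the choice of multilevel models and need not be a complete covariate list. Adjustment for co-interventions appears in another section, so the analysis section is not exhaustive. A journal article also commonly leaves covariates to a fuller document. This stands: an unadjusted model is not established.

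Nor is the trial too small or biased. The size is right without covariates, 466 were randomised against 3 × 135 = 405 needed, and the unadjusted standard error already allows for chance imbalance. This stands too.

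The gain may be slight. Recovery is rated against each worker's own baseline, so how strongly absolute baseline severity predicts it is unknown. A 50:50 recent/chronic split with a 20-point recovery gap would give an R² of only 0.04 to 0.06. The article nowhere states that the two kinds of worker differ in prognosis.

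It is tempting to ask for a recent-versus-chronic indicator. The article does not define one: the two-week window lies inside the six-month window, the criterion joins them with and/or, and time since onset is not listed as collected.

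What remains is that the article names no baseline symptom covariate for recovery, that suitable ones are measured, and that using them is likely to help and costs very little if it does not.

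**Conclusion.** An optional improvement, not an error. The unadjusted comparison is valid, and its stated size reproduces. Adjusting recovery for baseline pain and symptom days would add about 0 to 9 points of power at 80 evaluable per arm, starting from about 80%, with a loss of about one point if the covariates carry no information. With 93 per arm, the risk-difference approximation goes from 85.1% to 86.9–91.9% for R² of 0.05 to 0.20.

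The range depends on prognostic strengths that the article does not give, on the planned 80% and 60% recovery, and on calculations that ignore clustering by company. The upper end needs strong predictors and should not be taken as expected.

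**What to change.** State in the analysis plan that the multilevel model for recovery includes two prespecified fixed covariates:

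- T0 average pain intensity over the past four weeks;
- the T0 category of symptom days in the past six months.

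The article assesses recovery, pain and symptom days separately for the neck/shoulder and arm/wrist/hand regions, so each covariate should be for the same region as the recovery rating being analysed. Leave out a recent-versus-chronic indicator.

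Report the result as a difference in recovery percentage, standardised over all analysed workers, with its confidence interval, so that it can be read against the 20-point criterion. If an odds ratio is shown as well, label it as conditional on the covariates.

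The cost is a few sentences and a little more analysis work, with no new data. The covariates and their coding must be fixed before outcomes are examined by group.

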### Treatment allocation

An independent statistician prepared the randomisation by using a computer-generated randomisation. To prevent unequal randomisation, workers were pre-stratified by company and baseline sports participation assessed with the baseline questionnaire. Furthermore, block randomisation with blocks of three was used. The researchers prepared the envelopes containing the allocation to the intervention group and made two boxes with envelopes for each company. The first box contained the envelopes for workers who participated in sports activities (i.e. at least twice a week during at least 20 minutes at a moderate intensity level). The second box contained the envelopes for workers who did not participate in sports activities. Directly after the baseline measurements were completed the researchers opened the envelope and informed the worker about the group allocation. Workers who did not participate in the baseline measurements but sent their completed questionnaire and informed consent by post were randomised at the VU university medical center and informed about their treatment allocation by phone or by email.

### Sample size and participant flow

The main primary outcome variable in this study is self-reported recovery. The intervention will be considered successful if recovery from work-related neck and upper limb symptoms (i.e. completely recovered or much recovered) is 20% higher in the intervention group than in the control group. The number of participants in each group needed to detect a difference in recovery of 20% between the intervention group and the control group was ± 80, with α = 0.05 (two sided) and β = 0.20. This number was based on our expectation that recovery would be 80% in the intervention group and 60% in the control group. However, since we expected a loss-to-follow-up of 40%, ± 135 workers were needed in each group at baseline. Based on our pilot study we expected that 6.25% of our source population would participate in the study, which brings the minimum number of workers that needed to be invited for participation at 6480 workers. Figure 1 shows that approximately 8000 workers were invited to participate and that 466 workers were randomised into the trial.

